## Abstract

**Background:**

The health care situation of geriatric patients is often multifaceted, complex and often overlaps with social living conditions. Due to the lack of cross-sectoral and interprofessional health care geriatric patients often, receive insufficient care. Only a holistic view enables a comprehensive evaluation of the complex health risks, but also the potential to preserve the health of geriatric patients. The implementation of cross-sectoral, multi-professional case management could reduce the gaps in care, improve the autonomy of the geriatric patients in their own homes, and allow them to retain it as long as possible.

The “RubiN” project examines the effects of multi-professional, cross-sectoral and assessment-based case management on the quality of the care of geriatric patients. The results of the study aim to show whether geriatric patients receive better care using case management than patients who receive standard health care. In addition, data on the effects of case management on practices of general practitioners (GP), the satisfaction with the care concept amongst the case managers, patients and relatives will be collected. Furthermore, a health economic analysis will be carried out.

**Methods:**

The project is designed as a prospective controlled study and compares geriatric patients from practice networks in different regions in Germany. Inclusion criteria are: Age ≥ 70 years and care requirements from two different care complexes (identified with the screening instrument ‘Angelina’-questionnaire). The intervention is the use of a geriatric case management, where health care is organised based on patient-specific care requirements. Five practice networks of physicians will implement the intervention (*n* = 3200 patients) and three practice networks will serve as the control group (*n* = 1200 patients). The primary endpoint is the ability to manage activities of daily living, measured using the Barthel Index. The patients in the intervention group receive geriatric case management and the patients in the control networks receive standard care (“care as usual”). The analysis of the primary data, which is pseudonymised, occurs according to the intention-to-treat principle. For this purpose, the endpoints will be analysed using a group comparison after 12 months. For the health economic analysis, secondary data from the statutory health insurance providers will be included in the analysis, in addition to the primary data. Data for the analysis of the effects the concept has on the GP practices as well as on the satisfaction of the project participants will be collected with questionnaires and interviews with experts.

**Discussion:**

The implementation of cross-sectoral and interdisciplinary geriatric case management has been a topic of discussion for years, whereby positive effects have already been-shown. This planned study will be the first evaluation of the effect of case management for geriatric patients with a very large sample. In addition, the effects of case management on the GP practices and also on the relatives of the geriatric patients will be shown. It is intended that the study results pave the way for a widespread implementation of this concept.

**Trial registration:**

German Clinical Trials Register, ID: DRKS00016642. Registered on 29 October 2019 - Retrospectively registered.

## Background

The combination of a low birth rate and the high life expectancy of the cohort with the highest population among the intermediate age groups today (baby boomers = those born in the years from 1959 to 1968 [1]) is leading to major changes in the age structure of the German population. The number of elderly people is set to rise considerably. In 2013 there were already 4.4 million people aged 80 and over in Germany, which represented 5% of the population at the time. Their number will increase 40% by 2030 reaching 6.1 million, and in the year 2060 there will be in total approx. 9 million, which is about double the figure from 2013 [2]. Simultaneously, there will be a change in the prevalence of illnesses in Germany. For example, in comparison to 2007, a 20% increase in the prevalence of diabetes mellitus or a 41% increase in the prevalence of visual impairments in the German population is to be expected by 2050 [3].

These changes in the age structure of the population and in the prevalence of illnesses in Germany will have serious implications in terms of increased patient numbers, in particular with regard to age-related chronic illnesses and multimorbidity [4, 5]. A geriatric patient with multiple illnesses is often simultaneously affected by acute and chronic illnesses as well as functional limitations and is often at risk of being unable to remain in his/her own home.

The health care system in Germany, which to date has been highly sectored, and focused on physicians and acute inpatient care, does not meet the requirements of geriatric patients who need cross-sectoral care, also across professions, with a focus on the general practitioner (GP) [6].

### Case management for geriatric patients

Case management, which originated in the Anglo-Saxon countries, has also been introduced to and further developed in Germany since the 1990s. So far, there have been several projects dealing with case management based on the conditions in Germany [7]. The Advisory Council on the Assessment of Developments in the Health Care Sector (SVR) recommended the involvement of non-medical staff in the care of patients as early as 2007 [8].

In the AGnES project (community-based, e-health-assisted systemic support for primary care), for instance, it was shown that specially qualified caregivers and medical assistants can carry out tasks delegated to them by the GP to a high quality standard. This laid the foundation for the possibility to delegate tasks in GP practices, which has been possible since 2009 within the framework of standard care [9].

However, the implementation of case management in the German health care system is still slowly progressing, although e.g. the coordination and accordingly close monitoring of care are particularly important. The need for case management also arises from the increasing complexity of care of geriatric patients in various life situations and the complexity of the care structures in the German health care system. It is of particular importance that case management occurs across sectors and professions and not, as has been the case to date, health care is predominantly separated into outpatient and inpatient care and often uncoordinated. Case management’ goal is to guide each individual patient through the health care system, which often involves resolving complex issues and requires a high degree of coordination. This includes establishing contact with relevant service areas (e.g. social, health and insurance) and to steer efficiently the process of the provision of services. Thus, it involves continuous monitoring over a longer period of time and beyond the confines of the individual service areas.

The aim of case management is to ensure that the spectrum of tasks is carried out in close cooperation with the GP (ranging from the case intake, case assessment, goal and assistance planning, implementation and review of the help plan through to evaluation) [7]. Furthermore, it assures that the care situation is coordinated and that the retention or improvement of the independence of the geriatric patients in their own homes can be achieved.

Case management within the RubiN framework is not limited anymore to individual service providers. Instead, the individual service providers (GP practices) can access a joint pool of specially trained case managers within their network of physicians. In other words, the case managers are employed in the network of physicians and use a constantly expanding regional network, e.g. consisting of local facilities, care support points, social services, rehabilitation centres, physiotherapists, occupational therapists, support groups, nutrition counselling services, sports clubs, etc..

### Aims of the project

The main question of the RubiN project is whether multi-professional, cross-sectoral and assessment-based case management within the framework of a network of physicians improves the state of health of geriatric patients and their care situation in the network.

This question is to be examined on several levels (patient and relatives/ close personal contacts, service providers, practice networks) with different methods and evaluation endpoints.

The primary patient-level question is whether case management leads to patients in the intervention group being better able to manage activities of daily living after 12 months than those in the control group (primary endpoint: Barthel Index [10]).

At the level of relatives and close personal contacts, the objective is to determine whether the use of case management in the intervention group eases the situation and leads to greater satisfaction with regard to the care of geriatric family members.

The comparison between intervention group and control group in terms of the service providers is concerned with the effects of the intervention (case management). This includes the time taken between the identification of a care requirement and it being resolved, changes in terms of issues at the interface between different service providers, the satisfaction with the care situation and the quality of the teamwork, which is necessary due to the delegation of services.

At the level of the practice networks, the study explores whether the case managers’ curriculum corresponds with fulfilling tasks in the different networks. These tasks comprise whether diagnostic and care services can be assigned to the respective service providers (GP, specialist, case manager) based on a defined algorithm. It includes identifying barriers or beneficial factors due to networking of practices, or which proportion of the identified care services was able to be implemented after 12 months and by whom (GP, specialist, case manager, nursing services, etc.).

## Methods/ design

### Study design and procedure

The RubiN project is to be conducted as a prospective controlled intervention study in a clinical setting. Five practice networks, which are certified according to § 87b SGB V implement regionally adapted assessment-based case management. This certification of the practice networks provides a verification of special management skills [11]. The patients of the GP practices in these practice networks make up the intervention group. There are 640 patients per network, thus 3200 patients in total. Three further practice networks conduct the care of the patients as usual, without implementing case management. The patients of the GP practices in these three practice networks form the control group. It is comprised of 400 patients per network, thus 1200 patients in total (see Sample size calculation).

All patients receive the baseline assessment (BL) (see Table 1). In the intervention networks the patients included in the study then receive geriatric case management, designed according to patient-specific care requirements, for a period of 12 months. The patients in the control networks receive “care as usual”.

**Table 1 Tab1:** Outcome parameters for the levels (patients and relatives and close personal contacts)

Outcome	Measurement instrument/ operationalisation	Data collection point
**(A) Patient level**		
**(1) primary**		
Activities of daily living	Barthel Index	BL; FU12; FU21
**(2) secondary**		
Health situation with regard to geriatric aspects	ANGELINA screening	BL; FU12
Managing necessary daily tasks in the household	Instrumental activities of daily living (IADL)	BL; FU12
Mobility	Timed Up and Go, Tinetti’s mobility test	BL; FU12
Cognitive Abilities	DemTect	BL; FU12
Falls	Fall protocol	when/if a fall occurs
Quality of life	WHOQOL-OLD/ WHOQOL-BREF	BL; FU12
Malnutrition	Minimal Nutritional Assessment, MNA-Elderly	BL; FU12
Sociodemographic variables (age, gender, family background, further relevant sociodemographic data)	own design	BL; FU12; FU21
**(B) Level of relatives and close personal contacts**		
Easing of the burden	Burden Scale for Family Caregivers	BL; FU12
Sociodemographic variables (age, gender, family background, further relevant sociodemographic data)	own design	BL; FU12

*BL* baseline, *FU12* follow-up after 12 months, *FU21* follow-up after 21 months

After 12 months, an assessment is then carried out again, with all patients: the 12-month follow-up (FU12). For all patients who reach 21 months of participation within the duration of the project there is an additional collection of data on the primary endpoint (Barthel Index) (the 21-month follow-up (FU21)) (see Fig. 1).

**Fig. 1 Fig1:**
[figure not shown]
Project implementation plan

### Identification of eligible patients

In the GP practices that are participating in the practice networks a short questionnaire covering the most important geriatric topic areas will be completed for all patients who are aged 70 or over (e.g. regarding housing, assistance needs, medication, mobility, senses) (Angelina questionnaire [12]). If patients have assistance needs from two different topic areas they are eligible for the study and will be asked to participate in the project.

### Project participation, inclusion and exclusion criteria

#### Inclusion and exclusion criteria for participating practices

Inclusion criteria: The physician is working in a practice as an specialist for internal medicine, GP or specialist for general medicine and must be a member of the respective network of physicians (certified according to § 87b SGB V).

Exclusion criterion: GPs who work exclusively in a private practice.

#### Inclusion and exclusion criteria for participating patients

Inclusion criteria: geriatric patients: patients ≥70 years old with at least two geriatric feature complexes (i.e. ≥2 points in the ANGELINA-questionnaire from at least two different topic areas), a sufficient command of the German language.

Exclusion criteria: patients who are living in inpatient care facilities at the time of recruitment, patients with a terminal illness and/or using specialised palliative care (specialised palliative outpatient care, a hospice), patients with bipolar disorder or other severe psychiatric illnesses.

### Intervention

Health care professionals (qualified nurses, therapists or health care assistants (HCA)) receive the multiprofessional geriatric care training “GeriNurse” [13]. This is a 210-h training course (online and practical) and contains the following topics: health and project management, risk identification (preparation of clinical pathways), case management, risk management, accounting procedures, controlling, care management (regional neighbourhood management, public health, committee work).

Four case managers per practice network will receive the qualification, thus 20 in total for the RubiN project.

Based on the results of the patient’s baseline assessment the trained case managers perform a risk assessment. Based on the identified care requirements, patients are categorised as mild, moderate or severe cases. This provides the structure to determine the workload for the case managers in each case for the following 12 months (see Table 2) and a patient-specific, optimal treatment and/or care plan for the geriatric patient is prepared. The case managers monitor developments and progressions on a case-by-case basis, i.e. they make assessments and determine whether the care plan is to be followed or if it needs to be corrected or adjusted. The case managers identify care gaps and if required assess the care situation of these patients by means of case discussions and “round table” conferences. In doing so, they work closely with the GP and coordinate the care of the geriatric patients by being active across sectors and working with all other health professions in their respective practice network.

**Table 2 Tab2:**
[figure not shown]
Care-related workload per year for each patient, according to case severity

In addition, the case managers establish a network specifically for geriatric care in the regions, with appropriate communication and collaboration structures.

### Baseline assessment

The baseline assessment (BL) consists of measurement instruments which collect multidimensional data on the different aspects of geriatrics and the patient-relevant endpoints (see Table 1).

### Follow-up assessments

After 12 months, the 12-month follow-up assessment (FU12) takes place both in the intervention group and the control group. It uses the same measurement instruments as the baseline assessment. After a further 9 months, this is followed by the 21-month follow-up assessment (FU21) for the patients who reach this point within the duration of the project. Aside from the personal data of the patient only data related to the primary endpoint, the Barthel Index, is collected again.

### Sample size calculation

The number of cases was estimated for the primary endpoint (Barthel Index) of the RubiN project. The following parameter assumptions were made:
Error 1st type (α): 5%.Error 2nd type (β): 15% (≙ power of 85%)Effect size (d): 0.3Intervention/control ratio (on the patient level): 3/1Assumed intracluster correlation coefficient: 0.15Assumed drop-out rate: 33%

To demonstrate an effect of d = 0.3 with the mentioned assumptions, *n* = 534 participants are needed (400 in the intervention group and 134 in the control group). It is estimated that about 22 practices will participate in each practice network, each of which will be able to recruit an average of 30 participants. With an assumed intracluster correlation coefficient [14] of 0.15, a “design effect” of 5.5 for the regional design must be taken into account in the sample size planning. This increases the necessary sample size to *n* = 2937.

With an assumed dropout rate of 33%, 4384 (2937/0.67 = 4384) participants should be included, rounded up to 4400. The 5 intervention networks will each recruit about 640 participants (3200), the 3 control networks will each recruit about 400 participants (1200) (ratio 2.7:1, rounded up 3:1).

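### The design effect of 5.5 does not follow from 30 patients per practice and an ICC of 0.15 (5.35), and a practice size of 30 does not fit the control networks or the analysed sample

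*Protocol article*

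**What the plan says.** All the figures stand in the Sample size calculation of the protocol article. The inputs are a type I error of 5%, 85% power, an effect size of 0.3, a 3:1 ratio, an intracluster correlation of 0.15 and 33% dropout.

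- Before clustering, "534 participants are needed (400 in the intervention group and 134 in the control group").
- For the clusters, the article's estimate reads: "about 22 practices will participate in each practice network, each of which will be able to recruit an average of 30 participants".
- From this and the correlation of 0.15, "a “design effect” of 5.5 for the regional design must be taken into account in the sample size planning", which raises the number to 2937. No formula is given.
- Dropout is added last: "4384 (2937/0.67 = 4384) participants should be included, rounded up to 4400".
- Recruitment is then divided by network: "The 5 intervention networks will each recruit about 640 participants (3200"), and "the 3 control networks will each recruit about 400 participants (1200"). Study design and procedure repeats 640 and 400 per network.

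**The concern.** The paragraph prints both the inputs and the result of the clustering step, so the step can be checked from the article alone, and three things do not fit.

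1. The standard design effect for the printed inputs is not 5.5.
2. The stated number and size of practices cannot both hold in the control networks, given the recruitment planned there.
3. The practice size is described as a recruited number, but the design effect multiplies a number of analysed patients, because dropout is added only afterwards.

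The required number and the 85% power both rest on this design effect. In a clustered comparison the number of practices in the smaller arm matters a good deal for precision, and the article leaves it open whether a control network has about 13 or about 22 practices.

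**Working it through.** **Inputs**, all from the Sample size calculation: two-sided α = 0.05 (the article does not state the sides; two-sided reproduces its figure, one-sided gives 428), power 0.85, d = 0.3, ratio 3:1, ICC = 0.15, m = 30 per practice, 22 practices per network, 33% dropout, 5 × 640 = 3200 and 3 × 400 = 1200 recruited.

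**1. The plan's own chain**

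- Unclustered: control n = (1.960 + 1.036)² × (1 + 1/3) / 0.3² ≈ 133. Rounded up this is 134 + 402 = 536, against 534 stated. With 400 and 134 patients the power is about 85%, so 534 reproduces.
- Clustering: 534 × 5.5 = 2937, as stated.
- Dropout: 2937 / 0.67 = 4383.6, that is 4384, as stated.

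The multiplications are correct. The only figure in question is 5.5.

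**2. The design effect**

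- Standard formula: 1 + (m − 1) × ICC = 1 + 29 × 0.15 = 5.35.
- 1 + m × ICC = 1 + 30 × 0.15 = 5.50, which is the stated value.
- With 5.35: 534 × 5.35 = 2856.9, about 2857 analysed; 2857 / 0.67 = 4264.2, about 4265 recruited.
- Differences: 2937 − 2857 = 80 and 4384 − 4265 = 119, each about 2.7% of the stated figure.

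**3. Practices against recruitment**

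- 22 × 30 = 660 per network.
- Intervention: 640 / 22 = 29.1 per practice, which agrees with an average of 30.
- Control: 400 / 22 = 18.2 per practice, which does not. At 30 per practice, 400 / 30 = 13.3 practices would be enough.

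**4. Recruited against analysed size**

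- If 30 are recruited per practice, 30 × 0.67 = 20.1 are analysed. The design effect is 1 + 19.1 × 0.15 = 3.87 (3.865 before rounding), and 534 × 3.865 ≈ 2064 analysed patients are needed.
- With 22 practices in every network, intervention: 640 × 0.67 / 22 = 19.5 analysed, design effect 3.77.
- Control: 400 × 0.67 / 22 = 12.2 analysed, design effect 2.68.

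**5. Practice-level power of the planned recruitment**

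Analysed patients: 3200 × 0.67 = 2144 and 1200 × 0.67 = 804. Power = Φ(0.3 / √(DE_I/2144 + DE_C/804) − 1.96), where DE_I and DE_C are the design effects of the intervention and control arm.

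| Analysed per practice (intervention / control) | DE_I / DE_C | Power |
|---|---|---|
| 30 / 30 | 5.35 / 5.35 | 0.88 |
| 20.1 / 20.1 | 3.87 / 3.87 | 0.96 |
| 19.5 / 12.2 | 3.77 / 2.68 | 0.99 |

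Every row assumes equal practice sizes within an arm, even dropout and no variance between networks.

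**The case against.** The article gives no formula, so an omitted −1 is an inference. It speaks of an average of 30, so practice sizes may vary. The usual form for unequal sizes, 1 + ((1 + CV²) × 30 − 1) × 0.15 = 5.35 + 4.5 × CV², where CV is the coefficient of variation of practice size, reaches 5.5 at a CV of only about 0.18. Rounding up, or a practice size of 31, would also explain 5.5. This stands as far as the cause of the discrepancy goes. It does not rescue the text, which mentions no allowance for unequal sizes and no rounding at this step, although it declares its rounding of 4384 and of the ratio 2.7:1.

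It is also fair that 22 practices of 30 is an estimate of what practices can recruit. The product over eight networks, 8 × 660 = 5280, is therefore not a rival target to 4400, and capacity above target is no error. In the intervention networks there is no conflict at all. What remains is that the control networks cannot have both 22 practices and an average of 30 each when 400 are recruited.

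Using the recruited size in the design effect is a common simplification on the safe side. That is true, but the resulting 85% then does not describe the plan as printed.

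Three stronger readings are tempting, and the article supports none of them:

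- *The trial is too small.* Each correction lowers the required number.
- *The true power is 99%.* That figure holds only with equal practice sizes and no network variance. The arms are whole networks, five against three, and the article gives no network-level correlation.
- *The surplus was planned as a reserve for differences between networks.* The article calls the design effect one for the regional design, but the only practice or network quantities it gives for it are practice size and one correlation. It states no such reserve.

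**Conclusion.** The concern holds in a limited form. The stated design effect exceeds the standard value for its printed inputs (5.5 against 5.35), and 2937 and 4384 inherit the excess. They are correct products of 5.5, but about 2.7% above what the inputs give (2857 and 4265). The error is small and conservative.

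The practice size is the more consequential part. An average of 30 from 22 practices fits the intervention arm (29.1) but not the control arm (18.2, or about 13 practices of 30), and it is a recruited size applied to analysed patients. Depending on which practice size is meant, practice-level power for the planned recruitment lies between 0.88 and about 0.99, not at the stated 0.85. This range rests on d = 0.3, an ICC of 0.15, equal practice sizes within each arm, even dropout of 33% and no network-level variance. It describes practice-level clustering only and is not an estimate of the trial's actual power.

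**What to change.** In the Sample size calculation:

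1. Correct 5.5 to 5.35 and restate 2857 analysed and 4265 recruited, or state the formula or the practice-size variation that yields 5.5.
2. Give the number and average size of practices separately for intervention and control networks, so that they agree with 640 and 400 per network.
3. Restate the practice-level design effect and power by arm from analysed practice sizes (19.5 and 12.2 if every network has 22 practices), and say that the power assumes equal practice sizes and no variance between networks.

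Keep the target of 4400. Do not describe the surplus as a planned reserve for network variance; nothing in the article shows that it was planned as one or that it would be adequate.

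The cost is the rewording of one paragraph, with no change to recruitment or analysis.

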### Limitations

This project constitutes a regional comparison. This is statistically not as robust as a grouping by randomisation at the patient level (RCT). An RCT was not possible here as the intervention is implemented as a regional structure.

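### The design effect of 5.5 covers clustering in practices only; allocation is by whole network (5 versus 3), so the stated 85% power for d = 0.3 is not supported and is lost at small between-network variation

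*Protocol article*

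**What the plan says.** Under *Sample size calculation*, the protocol article assumes a 5% type 1 error, 85% power, d = 0.3, a 3:1 patient ratio, one ICC of 0.15 and 33% dropout. It derives 534 patients before clustering (400 and 134). It then expects "about 22 practices will participate in each practice network, each of which will be able to recruit an average of 30 participants", and states that a design effect "of 5.5 for the regional design must be taken into account in the sample size planning". The total becomes 2937, then 4384 after dropout, rounded to 4400: five intervention networks of about 640 and three control networks of about 400.

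Under *Study design and procedure*, five networks implement case management, while "Three further practice networks conduct the care of the patients as usual, without implementing case management". *Limitations* gives the reason: "An RCT was not possible here as the intervention is implemented as a regional structure". *Data analysis* (patient level) plans multilevel models that take account of differences among providers and among networks.

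**The concern.** The clustering that matters most for power is at the level at which treatment is assigned. Here that is the network. Every patient and practice in a network is in the same arm, so any difference between networks in outcome level (region, local services, staffing, case mix) goes straight into the difference between arms. Adding patients or practices inside the same eight networks does not average it out.

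The calculation names one cluster size, the practice, and calls the result a design effect for the regional design. A reader would take the regional allocation as covered, and it is not. The planned analysis recognises a network level that the sample size leaves out.

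The primary result is at stake. A null finding on the Barthel Index would be read against 85% power, in a project meant to inform transfer to standard care.

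**Working it through.** **Reproducing the plan's figures**

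- Before clustering, two-sided 5%, 3:1 ratio: control n = (1 + 1/3) x (1.960 + 1.036)² / 0.3² = 133.0, so 134. Intervention = 3 x 134 = 402. Total 536, against 534 stated. At 400 and 134, SE = √(1/400 + 1/134) = 0.0998, 0.3/0.0998 = 3.006, and power is 85.2%. The article does not state sidedness; one-sided alpha gives 428 and does not fit.
- Clustering: 1 + 30 x 0.15 = 5.5, and 534 x 5.5 = 2937. The usual 1 + (30 − 1) x 0.15 = 5.35 gives 2857, so the plan is slightly conservative here.
- Dropout: 2937/0.67 = 4384.

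The arithmetic holds, and no network term appears anywhere. Nor can 0.15 be read as a regional ICC: at 4400/8 = 550 patients per network the design effect would be 1 + 549 x 0.15 = 83.35.

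**Adding the network level**

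Inputs from the article: 5 and 3 networks; 0.67 x 3200 = 2144 and 0.67 x 1200 = 804 analysed patients; total within-practice correlation 0.15; d = 0.3 with SD 1. Assumptions: the network ICC ρ (correlation between patients of one network in different practices), shown from 0 to 0.05, and an unadjusted comparison.

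Variance of the arm difference = ρ(1/5 + 1/3) + (0.15 − ρ)(1/P_I + 1/P_C) + 0.85(1/2144 + 1/804), where P_I and P_C are the numbers of practices per arm. The last term is 0.00145 throughout.

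Practice numbers depend on how 30 per practice is read:

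- 30 recruited: P_I = 3200/30 = 106.7, P_C = 1200/30 = 40 (about 20 analysed per practice).
- 30 analysed: P_I = 2144/30 = 71.5, P_C = 804/30 = 26.8.

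Power is given with a normal reference and with a noncentral t on 5 + 3 − 2 = 6 degrees of freedom.

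| Practice size | ρ | Network term | Practice term | Variance | SE | Power, normal | Power, t on 6 df |
|---|---|---|---|---|---|---|---|
| 30 recruited | 0 | 0 | 0.00516 | 0.00661 | 0.081 | 96% | 86% |
| | 0.01 | 0.00533 | 0.00481 | 0.01160 | 0.108 | 80% | 64% |
| | 0.02 | 0.01067 | 0.00447 | 0.01659 | 0.129 | 64% | 50% |
| | 0.05 | 0.02667 | 0.00344 | 0.03156 | 0.178 | 39% | 30% |
| 30 analysed | 0 | 0 | 0.00770 | 0.00915 | 0.096 | 88% | 74% |
| | 0.01 | 0.00533 | 0.00718 | 0.01397 | 0.118 | 72% | 57% |
| | 0.02 | 0.01067 | 0.00667 | 0.01879 | 0.137 | 59% | 45% |
| | 0.05 | 0.02667 | 0.00513 | 0.03325 | 0.182 | 38% | 28% |

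**Where 85% is lost**

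- Normal reference: once ρ exceeds about 0.007 (30 recruited) or 0.002 (30 analysed).
- t on 6 df: once ρ exceeds about 0.0006 (30 recruited); never reached with 30 analysed.
- With unlimited patients and practices in these eight networks, only ρ x 8/15 remains. On the normal reference, 85% needs an SE of at most 0.3/2.996 = 0.100, so ρ of at most 0.0100 x 15/8 = 0.019. On 6 df the limit is about 0.013.

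**The case against.** **The network ICC is not in the article.** This is right. No value between 0 and 0.05 can be called likely on this evidence, and at ρ = 0 three of the four series above exceed 85%. A reader might infer that the 85% is simply not delivered, or that the trial has about even odds of detecting its target. The article supports neither statement: the first fails at zero network variation, and the second amounts to choosing ρ near 0.02.

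**The 6 degrees of freedom are an assumption.** This is also right. The reference distribution is normally fixed in an analysis plan, which is not shown. But the point does not depend on it: with a normal reference, power still falls to 72–80% at ρ = 0.01 and 59–64% at 0.02.

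**Practice sizes are ambiguous.** If 22 practices are placed in every network, power is higher: 84% (normal) and 70% (6 df) at ρ = 0.01. That reading gives 400/22 = 18 recruited per control practice, which does not fit the stated 30, so it is not used above.

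**Baseline adjustment could recover power.** The Barthel Index is measured at baseline and multivariate models are planned. If baseline correlated 0.7 with follow-up and reduced every component equally, the variance would be multiplied by 1 − 0.49 = 0.51. At ρ = 0.02 power would then be 87–90% (normal) and 72–78% (6 df). This is a real possibility, but the stated calculation does not use it, and neither the correlation nor an equal reduction at network level is given.

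**The network level is in the analysis and the regional design is disclosed.** Both are true. But each network lies wholly in one arm, so modelling networks makes the uncertainty visible without removing it. *Limitations* concedes less robustness than patient-level randomisation but does not say that the comparison rests on eight units or that the power is conditional.

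**Conclusion.** The point holds in this form: the 85% power for d = 0.3 is not supported, because it requires between-network variance of practically zero and the article neither states nor justifies that. The article's own description (different regions, regionally adapted case management, usual care that depends on local standards, finances and staffing) gives no reason to expect zero.

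Across both practice-size readings, power at a network ICC of 0.01 is 72–80% (normal) or 57–64% (6 df); at 0.05 it is 38–39% or 28–30%. These figures rest on an assumed ICC range, the stated within-practice correlation of 0.15, 33% dropout and no baseline adjustment. They show how sensitive the claim is. They do not estimate the trial's actual power.

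**What to change.** Keep the recruitment targets. In *Sample size calculation*:

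- Replace the single design effect with a three-level calculation (patient, practice, network) for 5 and 3 networks. Use practice sizes consistent with 640 and 400 patients per network, and say whether 30 per practice means recruited or analysed.
- Report power, or the detectable effect, over a range of network ICCs such as 0, 0.01, 0.02 and 0.05, with a small-sample reference suited to eight networks. If baseline adjustment is to be counted on, state the assumed correlation.
- Remove the unqualified 85%, and no longer describe 5.5 as covering the regional design.

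In *Limitations*, state that the allocation unit is the network (n = 8), and that more patients within these networks do not reduce between-network variation.

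The cost is one rewritten paragraph, one added sentence and a less favourable stated power. No extra patients are needed, and neither the endpoint nor the planned model changes.
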